#### Population-Level Analysis

Phased implementation provides an opportunity to examine trends in acute care use using administrative data for the target population as a whole. With increased reach of C2C in Calgary with each phase, the proportion of the target population exposed to C2C will increase over time, and, if successful, acute care use in this population will, on average, decrease over time. We will select a population of patients from administrative health data who present to a Calgary acute care facility and meet the following criteria: ≥ 18 years of age; ED visit or hospital admission with an associated ICD-10 Z59x diagnosis (problems related to housing and economic circumstances); ≥ 3 ED presentations, or ≥ 2 hospitalizations within the past year; and at least one high-risk health condition, as defined by ICD-10 diagnostic codes corresponding to C2C enrolment criteria.

Beginning 6 months prior to C2C program implementation, and continuing for 12 months beyond enrolment end date (i.e., May 2015–December 2020), we will retrospectively ascertain the following every 3 months: total number of patients meeting eligibility (per administrative data as above); proportion of patients currently or previously enrolled in C2C (per program data); acute care use for the prior 12 months. We will inspect the number of eligible patients enrolled in C2C over time to ensure our increased enrolment assumption is correct. We will use a generalized linear modeling framework to assess the trend over time, in both the total number of eligible patients in administrative data (to assess change in the absolute number) and average acute care use (to assess change in use among those who meet criteria), measured at 3-month intervals. We will adjust for age, sex and defined health conditions.

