#### Power Calculation

We calculated power for the within-subject comparison for the primary outcome of ED visit rate over 12 months. Under ideal conditions intensive case management with outreach may reduce ED visits by 30% in high users (18). Assuming a mean pre-intervention rate of 9.3 visits/year (as noted for Phase 1 patients) and a post-intervention rate of 6.5 visits/year, a common standard deviation of 10, and a correlation between paired observations of 0.05, a sample of 257 individuals will provide more than 90% power to detect a difference at the 5% level of significance. Note that if the correlation increases, the power will increase, hence our choice of a low correlation. We have a waiver of consent to access administrative health data; therefore all patients that engage with the C2C team are eligible for inclusion in the administrative data analysis. Given our use of administrative data with full capture for participants in Alberta, any loss to follow up will be due to outmigration or invalid personal health insurance numbers. Despite this expected attrition, with 249 engaged patients in July 2018, by end of 2019, we will have an adequate study sample to detect meaningful differences.

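### The population-level average is taken over the same 12 months that define eligibility, so patients who improve past the thresholds leave it and a true reduction is attenuated

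*Protocol article*

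**What the plan says.** The Population-Level Analysis section of the protocol article selects adults with a housing-related diagnosis code who have "≥ 3 ED presentations, or ≥ 2 hospitalizations within the past year; and at least one high-risk health condition". From May 2015 to December 2020, "we will retrospectively ascertain the following every 3 months: total number of patients meeting eligibility", together with the "proportion of patients currently or previously enrolled in C2C (per program data") and "acute care use for the prior 12 months". Two trends are then modelled. The one at issue here is "average acute care use (to assess change in use among those who meet criteria), measured at 3-month intervals". Its companion, a simple head count per quarter, is "the total number of eligible patients in administrative data (to assess change in the absolute number"). Adjustment is for age, sex and defined health conditions. The stated expectation, as coverage grows, is that "if successful, acute care use in this population will, on average, decrease over time".

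**The concern.** The entry rule and the outcome use one look-back of 12 months, and membership is decided afresh each quarter. A fixed cohort is not a plausible reading, because the number eligible is itself a quarterly outcome. The average is therefore cut off from below by its own entry rule. A patient who drops under both the ED and the hospitalization threshold does not count as a low value; that patient is no longer counted. Adjusting for age, sex and health conditions cannot undo selection on the outcome, and the Discussion does not list this among the limitations.

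The exposure measure has the same weakness. Enrolled patients who improve past the thresholds leave the eligible set, so the share ever enrolled understates reach, and more so the better the program works.

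This is one of the three approaches to effectiveness. A working program could show a weak trend in the quantity to which the expectation is attached.

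**Working it through.** **The protocol's own figure.** The only power statement concerns the within-subject comparison. The SD of the difference is √(2 × 10² × (1 − 0.05)) = 13.78. With a difference of 9.3 − 6.5 = 2.8 and N = 257, two-sided 5%, power is 90.3% (normal) or 90.0% (noncentral t). It reproduces and is not in question. No figure is given for the population-level analysis.

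**Inputs.** From Power Calculation: a mean of 9.3 visits per year, and the premise that "intensive case management with outreach may reduce ED visits by 30% in high users". From Population-Level Analysis: the threshold of 3 ED visits. Assumed: negative binomial counts with dispersion 1 or 2, and exposure of 20% or 100%. The hospitalization route is not modelled.

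**Calibration.** Choose the source mean μ so that E[X | X ≥ 3] = 9.3. This gives μ = 6.30 (dispersion 1) and 4.46 (dispersion 2). Dispersion 1 can be checked by hand: the distribution is geometric, so E[X | X ≥ 3] = 3 + μ = 9.3.

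**A 30% cut for everyone, dispersion 1.** Each visit is kept with probability 0.7, so μ becomes 4.41.
- Share still at 3 or more: (4.41/5.41)³ ÷ (6.30/7.30)³ = 0.5417/0.6428 = 0.843. The number eligible falls 15.7%.
- Average among those still eligible: 3 + 4.41 = 7.41, and 7.41/9.3 − 1 = −20.3%.
- Everyone retained: 9.3 × 0.7 = 6.51, which is −30%.

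**A 30% cut in 20% of eligible patients, dispersion 1.**
- Relative number eligible: 0.8 + 0.2 × 0.8427 = 0.9685.
- Average: (0.8 × 9.3 + 0.2 × 0.8427 × 7.41)/0.9685 = 8.97, which is −3.5%.
- Everyone retained: −0.2 × 30% = −6.0%.
- Share ever enrolled among those still eligible: 0.2 × 0.8427/0.9685 = 17.4%, against a true 20%.

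**Benefit only near the threshold, dispersion 1.** Patients with 3 to 5 visits are 35.7% of the eligible, with a mean of 3.90. Let a quarter of them fall below the threshold and nobody else change.
- Relative number eligible: 1 − 0.25 × 0.357 = 0.911.
- Average: (9.3 − 0.25 × 0.357 × 3.90)/0.911 = 9.83, which is +5.7%.

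**Results over dispersion 1 to 2**

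| Scenario | Everyone retained | Average among eligible | Number eligible | Count × average |
|---|---|---|---|---|
| 30% cut, 100% exposed | −30% | −19% to −20% | −16% to −18% | about −33% |
| 30% cut, 20% exposed | −6.0% | −3.2% to −3.5% | −3.1% to −3.5% | −6.6% |
| A quarter of those with 3–5 visits exit | not fixed by the scenario | +5.7% to +6.4% | −8.9% to −9.9% | −3.7% to −4.1% |

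**Other patterns of benefit**, by simulation at full exposure with negative binomial shape 0.3 to 1.0 (the inverse of dispersion):

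| Pattern | Everyone retained | Average among eligible | Number eligible |
|---|---|---|---|
| 30% of patients stop visiting | −30% | −3% to −4% | −24% to −26% |
| Rate × 0.3 in those with 3–5 visits only | −12% | +8% to +10% | −19% to −20% |
| Rate × 0.6 in those with ≥ 10 visits only | −24% to −25% | −22% to −23% | about −1% |

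**The case against.** The strongest reply is that the average is only half of the planned analysis. The same sentence also models the number of eligible patients, and a patient who falls below the thresholds lowers that number. Read together, the two trends show benefit in each of the first three scenarios: even where the average rises by 5.7% to 6.4%, the count falls by 8.9% to 9.9% and their product by 3.7% to 4.1%. A rule for joint reading could also sit in an analysis plan that is not shown. This stands, and it limits the point to the average itself. It does not repair the average, and the stated expectation remains worded as a fall in average use.

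A reader might infer that a successful program would be expected to show a rising average, or that the population-level analysis as a whole would read it as a failure. The document does not support either. Under its own 30% premise the average still falls. A rise needs benefit concentrated in patients just above the threshold; where benefit lies in patients with 10 or more visits, attenuation is slight. A patient who goes from 20 visits to 8 stays in the average and lowers it.

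The sizes also rest on assumptions. Exposure is not stated. The mean of 9.3 comes from program patients, not from the administrative population. The fitted SD among the eligible is 6.8 to 7.5, not the 10 used for power. Patients who stay eligible through hospitalizations are not modelled.

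**Conclusion.** The point holds for the average: it is conditioned on its own outcome window, and every scenario examined showed attenuation, ranging from slight to severe. With a uniform 30% cut, about a third or more of the effect is lost at full exposure (19% to 20% seen against 30%) and over 40% at 20% exposure (3.2% to 3.5% against 6.0%). A wrong sign is possible, not expected. The direction follows from the stated definitions; the sizes depend on the assumed distribution and exposure. The analysis is supportive, and neither the powered within-subject comparison nor the matched cohort is touched, so this should be fixed but does not threaten the primary result.

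**What to change.** At each quarter t, define the eligible set from months t − 12 to t. Measure acute care use in the following period for everyone in that set, whether or not they still meet a threshold, and compute the share ever enrolled on the same set.

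This removes the shared window, but sets re-selected each quarter still lose patients who improved earlier. So also model total acute care visits in the target population (count × average), or use over a denominator not defined by recent use. The second is cleaner: count × average omits the remaining visits of those who exit, which is why it gives −6.6% above where the truth is −6.0%. State that the average is interpreted only jointly with the number eligible, and reword the expectation accordingly.

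The cost is re-programming on the same administrative extract. Within the stated window, the series loses its last quarter if the outcome is next-quarter use, or about its last four quarters if it is use over the next 12 months.

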#### Power Calculation

We calculated power for the within-subject comparison for the primary outcome of ED visit rate over 12 months. Under ideal conditions intensive case management with outreach may reduce ED visits by 30% in high users (18). Assuming a mean pre-intervention rate of 9.3 visits/year (as noted for Phase 1 patients) and a post-intervention rate of 6.5 visits/year, a common standard deviation of 10, and a correlation between paired observations of 0.05, a sample of 257 individuals will provide more than 90% power to detect a difference at the 5% level of significance. Note that if the correlation increases, the power will increase, hence our choice of a low correlation. We have a waiver of consent to access administrative health data; therefore all patients that engage with the C2C team are eligible for inclusion in the administrative data analysis. Given our use of administrative data with full capture for participants in Alberta, any loss to follow up will be due to outmigration or invalid personal health insurance numbers. Despite this expected attrition, with 249 engaged patients in July 2018, by end of 2019, we will have an adequate study sample to detect meaningful differences.

### Patient, Staff, and Partner Experience

We will use multiple data sources to explore experience with the C2C program: semi-structured interviews of patients, C2C staff and operational leads, program partners (hospital and community agency staff who refer to and work with the C2C team), and decision makers (health system and community leaders), as well as field observations of the C2C team. Semi-structured interviews with multiple populations provide a unique opportunity to identify unexpected barriers and experiences not captured in surveys (45), while field observations provide an opportunity to observe the team's daily activities.

#### Interviews

We will conduct patient, staff and partner interviews at various time points after program launch. Purposive sampling of interview subjects will ensure broad representation of axes of social vulnerability (e.g., housing status, age, gender, and ethnicity) and personal experiences, both working within, and in partnership with C2C, respectively (46). All recruitment will occur by invitation. The final number of interviews will depend on the variability of responses, and recruitment will continue until theoretical saturation is reached (47, 48), (i.e., when no new meaningful concepts arise from the data). We anticipate we will require between 20 and 30 patient interviews and 30–40 staff and partner interviews (given the diversity across agencies) (49, 50). All interviews will be conducted in a private space (e.g., partner office) and location convenient to the participant. Interviews will be in-person or *via* telephone, semi-structured, and follow an interview guide tailored to the individual being interviewed (i.e., patient, staff, program partner or decision maker). Interviews will explore how participants interact with the program, positive and negative experiences, impact of C2C, perceptions on the services provided, and other contextual factors of influence.

#### Field Observations

A researcher will observe C2C team members during their routine workday, taking brief notes that are translated into comprehensive field notes. Recorded data will focus on team member activities, dialogue, physical spaces, interactions with clients and partners, and interactions among team members. Observations, each 3–4 h in duration, will sample different days of the week, times of day, and different team members including nurses, health navigators, and managers. While patient interactions will be the primary focus, team meetings, both formal and informal, as well as office work, will also be sampled.

### Qualitative Data Analysis

Facilitated by NVivo software, we will use thematic analysis to analyze interview transcripts and observation field notes (51). A research associate trained in qualitative methods will use data and theory-driven coding (51), to develop a preliminary codebook (52). Theory driven codes will be derived from the conceptual framework of structure, process and outcome. Data-driven codes will include emerging ideas, patterns, and concepts in the data that are not captured by the theory-driven codes. The codebook will consist of codes clustered into overarching themes and will include code names, their definitions, inclusion and exclusion criteria, and examples of text. The research team will review the preliminary codebook to discuss the interpretation and application of the codes and whether the themes capture the conceptual framework. The codebook will then be used by at least two analysts to independently code a sample of transcripts; analysts will have the ability to add new codes if they identify emerging codes. The research team will meet frequently to resolve discrepancies in coding and come to an agreement regarding the definitions of the codes and how they should be applied. The codebook will be updated as required throughout. Inter-rater reliability (IRR) tests will be performed on a sample of transcripts that have been independently coded but not yet discussed. When IRR tests reach a kappa of 360, remaining transcripts will be coded by one analyst and discussion will be restricted to new codes.

A codebook will help in managing the large amount of data from different sources (interviews and observations), promote consistency amongst coders (53), and enhance data understanding and interpretation. We will enhance the trustworthiness of our analysis through triangulation (examining data from several sources and perspectives). We will account for participants' social roles (staff, managers, patients, program partners, and decision makers), demographics, and the professional, academic and experiential backgrounds of researchers involved.

### Data Integration, Model Refinement and Understanding Across Structure, Process, and Outcome

While we will analyze quantitative and qualitative data in parallel, methodological triangulation will focus specifically on validating and refining our program model and gaining a richer understanding of how individual components are linked within context, by comparing and contrasting our findings across data sources (54, 55). To do so, we will systematically examine the components of our program model against our evaluation findings, looking for areas of confirmation, expansion or discordance between both the existing model and new findings, and across data sources. Any discordance will be explored narratively.

### Cost Effectiveness

We will perform a cost-utility analysis with a 1-year time horizon, from the perspective of the publicly funded health care system, comparing the C2C program to usual care. The analysis will follow guidance from the Canadian Agencies for Drugs and Technologies (CADTH) (56). Direct patient level health care costs will be obtained from Alberta Health Services (12 months prior to and following program enrolment): hospital admissions, ED visits, urgent care visits, ambulatory care, substance use treatment programs, medication and physician costs. Hospital costs are based on facility-specific costs per day and include direct and indirect costs such as diagnostic imaging, laboratory, housekeeping, administration, etc. Monthly total health care costs will be calculated per patient by summing across available cost data. Program costs will be obtained from the operational budget: wages, training, transportation, management, and IT costs. Health outcomes of interest will be lives lost and the change in health-related quality of life (measured by the EQ-5D). Utility will be derived from EQ-5D data using Canadian based preferences (57). A linear extrapolation of utilities over time will be used to calculate per patient quality-adjusted life years (QALYs).

#### Cost Analysis

A generalized linear model with random effects controlling for time and patient characteristics such as age and sex will be used to estimate mean health care costs pre- and post-enrolment (58). The difference in health care costs between the pre- and post-enrolment periods will be calculated and compared to program costs.

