**Figure 1 F1:**
[figure not shown]
Program implementation and study timeline.

To be eligible for the program, patients must be ≥ 18 years of age, homeless or unstably housed (38), have ≥ 3 ED presentations, or ≥ 2 hospitalizations within the past year. While definitions of high acute care use vary, we chose the most conservative definition (18) in order to make the program inclusive and allow refinement to occur over the initial phases of implementation. Preliminary data gathered for the first 127 patients referred to the program before expansion indicates that, on average, C2C patients had 9 ED visits in the year prior to referral and 20% had a hospital admission. The most common reasons for admission were cellulitis, sepsis, pneumonia, substance use and other mental health diagnoses. C2C patients were more likely to be male (66%), 29% identified as Indigenous, 88% used substances and 78% were homeless. Referrals are accepted from acute care facilities, health clinics, and community agencies. Reasons for referral include attachment to primary care, housing support, connection to substance use treatment, advocacy, and discharge planning.

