### Measures of Effectiveness

#### Acute Care Use

We will use administrative health data to assess acute care use among C2C patients 12-months before and after enrolment: ED visits (primary outcome); hospital admissions; repeat ED visits within 72 h of discharge; unplanned readmissions within 30 days among hospitalized patients; total hospital bed days; deaths; ED and hospital discharge diagnoses; and ICU admissions. Data will be obtained by linking unique provincial health insurance numbers to administrative health data housed by Alberta Health Services.

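### The net-cost statement sets an uncontrolled pre/post cost difference against program costs, so a fall expected after selection on high use would count as savings

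*Protocol article*

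**What the plan says.** All references are to the protocol article.

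- **Cost Effectiveness** describes a one-year cost-utility analysis for the public payer, "comparing the C2C program to usual care". Patient-level health care costs are described only for the 12 months on either side of program enrolment, that is, for people who enrolled. It adds: "Health outcomes of interest will be lives lost and the change in health-related quality of life".
- **Cost Analysis** specifies "A generalized linear model with random effects controlling for time and patient characteristics such as age and sex" to estimate mean costs before and after enrolment. It then states: "The difference in health care costs between the pre- and post-enrolment periods will be calculated and compared to program costs".
- **The Connect 2 Care Intervention** (eligibility paragraph after Figure 1) requires that patients "have ≥ 3 ED presentations, or ≥ 2 hospitalizations within the past year".
- **Comparison Cohort** plans a propensity-matched control group from administrative data. It is used for acute care utilization and death rates; costs and QALYs are not mentioned.
- **Cost-Effectiveness** (the subsection on the ICER) plans a seemingly unrelated regression for costs and QALYs and names no comparator.

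**The concern.** The question posed is what C2C costs relative to usual care over the same year. The quantity in Cost Analysis is how much the same patients' costs changed after a year in which high use was the condition of entry. These coincide only if, without C2C, the next year would have cost as much as the qualifying year.

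That is unlikely. People selected because a fluctuating count was high will on average show a lower count next time. Referrals also come from acute care facilities, so enrolment can follow directly on an acute episode. In a one-group comparison the period contrast is the program effect plus this natural fall, and nothing in the data separates the two. Age and sex do not change between the periods in any way that could account for it. Calendar time removes secular trend, but the fall follows each patient's own entry date.

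At stake is the statement of whether the program pays for itself. The Discussion says the results will feed directly into decisions about C2C, and the error runs in the program's favour.

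**Working it through.** **1. The plan's own figure.** The article gives no cost figures and no precision statement for the economic analysis. Its one power figure is for the within-subject ED comparison (Power Calculation). Inputs: 9.3 visits/year before, 6.5 after, common SD 10, correlation 0.05, 257 patients, 5% level (taken as two-sided).

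- SD of the paired difference = 10 × √(2 × (1 − 0.05)) = 13.78
- Power = Φ(2.8 × √257 / 13.78 − 1.96) = 0.903 (paired t: 0.900)

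This agrees with the stated power of more than 90%. The arithmetic is sound; the issue is what a pre/post difference measures.

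**2. Expected fall with no program effect.** If use in successive years has the same mean mu and the same spread in the unselected source population, with correlation rho, linear regression to the mean gives

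expected fall = (1 − rho) × (9.3 − mu).

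The 9.3 is from Power Calculation. The long-run mean mu is not in the documents and is assumed to lie between 4 and 8. For rho, the plan's 0.05 is shown with assumed values of 0.5 and 0.7.

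| rho | mu = 8 | mu = 6 | mu = 4 |
|---|---|---|---|
| 0.05 (plan) | 1.2 visits (13%) | 3.1 (34%) | 5.0 (54%) |
| 0.5 (assumed) | 0.65 (7%) | 1.65 (18%) | 2.65 (28.5%) |
| 0.7 (assumed) | 0.39 (4%) | 0.99 (11%) | 1.59 (17%) |

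Worked example: at rho = 0.5 and mu = 6, the fall is 0.5 × 3.3 = 1.65 visits, and 1.65 / 9.3 = 18%.

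**3. Set against the effect sought.** The plan's target is 9.3 − 6.5 = 2.8 visits (30%). At rho = 0.05 that whole fall occurs with no program effect when mu = 9.3 − 2.8/0.95 = 6.35.

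**4. Limits of the illustration.** These are ED visits, not dollars. Cost Effectiveness also counts ambulatory care, medication, physician and substance use treatment costs, which are not entry criteria and need not fall in step. The formula calls for the correlation in the unselected population, whereas the plan's 0.05 refers to enrolled patients and was chosen low to be cautious about power. The first row is therefore an upper illustration, not a forecast.

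**The case against.** **Two analyses, not one.** Cost Analysis and Cost-Effectiveness are separate subsections. A reader might infer that the pre-enrolment year is the usual-care arm of the ICER, but no sentence says so. The ICER subsection names no comparator, and a condensed article may leave that to the full protocol. This stands, and it confines the point to the net-cost comparison, which the article does state.

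**Deaths.** A reader might infer that lives lost under usual care are zero by construction, because patients must be alive to enrol and Acute Care Use lists deaths among measures taken "to assess acute care use among C2C patients 12-months before and after enrolment". That would follow only if the economic analysis compared deaths pre versus post. The article does not say it does, and its one modelled comparison of death rates is with matched controls. The point is conditional only.

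**QALYs.** A reader might also expect a QALY bias in the opposite direction. None can be stated. EQ-5D is scheduled at 6 and 12 months after enrolment and is not named among the baseline items, so on this text no pre-year QALY can be formed.

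**Death shortening the cost period.** Costs are built up monthly and modelled with random effects and time, which can accommodate unequal follow-up. The article does not say that raw annual totals are compared regardless of death.

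**Disclosure and size.** Within-Subject Comparison and the Discussion acknowledge changes in health over time, time-varying confounders and the lack of randomisation. Mean prior use of about nine visits, well above the threshold of three, also suggests that many patients are persistent heavy users, which would make the fall smaller. Both are fair. But the disclosures do not name selection on prior use and give no remedy for costs, and a smaller fall would still be counted as savings.

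**Conclusion.** The concern holds for the net-cost statement in Cost Analysis. It sets an uncontrolled pre/post difference, in patients selected on high prior use, against program cost, while the declared comparison is with usual care. Whatever part of the fall would have happened anyway is counted as savings. This is a stated estimate that does not answer the stated question, not a detail left to a fuller document.

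The direction rests on selection by past-year use and on year-to-year use being less than perfectly stable. The amount in dollars cannot be derived from the article. The ED-visit figures (7% to 28.5% at rho 0.5, 13% to 54% at rho 0.05, for mu from 8 to 4) show only that the artefact could be comparable with the 30% effect sought. They should not be quoted as a share of cost. The article does not support extending the conclusion to the ICER, lives lost or QALYs.

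**What to change.** 1. Obtain costs for the matched cohort from the same administrative sources. Give each control an index date and require the same prior-use criterion at that date. Comparison Cohort now describes the source population by a housing-related diagnosis code and a Calgary visit, with no use threshold, so without this step the two groups could regress by different amounts.
2. Estimate incremental cost as C2C versus matched controls over the 12 months after the index date, adjusted for pre-index cost (or by difference-in-differences), with death and censoring handled identically in both groups.
3. Set that estimate against program cost. Keep the pre/post difference and label it descriptive.
4. State that deaths in the economic analysis come from the comparison with matched controls.
5. Name the comparator for the ICER. EQ-5D is planned for C2C patients only, so the matched cohort cannot supply usual-care utilities. State their source as an assumption, with sensitivity analysis.

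The cost is one further extract for a cohort already planned, plus revised analysis wording. The interval will be wider and the estimated savings probably smaller. Unmeasured confounding, already acknowledged in the Discussion, remains.
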